## Abstract

**Background:**

Neonatal unit (NU) admissions for premature babies can last for months, which can significantly impact parental mental health (MH) with symptoms of depression, stress, and anxiety. Literature suggests fathers experience comparable MH symptoms to mothers. Family integrated care (FICare) is a culture where parents are collaborators and partners in caring for their hospitalized newborns. FICare improves infant outcomes and maternal MH. Similar reports on fathers are limited.

**Objective:**

The primary aim of this study is to investigate the impact of supporting father or partner engagement in FICare of preterm infants on their MH up to 6 weeks postdischarge. The secondary aim is to investigate the impact on maternal MH.

**Methods:**

This is a 2-phase study: phase 1 to gather baseline information and phase 2 to assess the impact of enhanced father or partner engagement in FICare on their MH, involving 2 NUs (tertiary and level 2). Enhanced FICare will be developed and introduced (eg, information booklet, workbook, classes, and a father peer-support group) alongside standard FICare practices. Father or partner MH will be assessed with semistructured qualitative interviews and validated questionnaires: Generalized Anxiety Disorder Assessment, Patient Health Questionnaire, and Parental Stressor Scale: Neonatal Intensive Care Unit from NU admission to 6 weeks postdischarge. Mothers will be assessed by focus groups and the same questionnaires. Descriptive statistics and appropriate comparative tests, such as the 2-tailed *t* test, will be used to analyze and compare phase 1 and 2 data. Qualitative data will be coded line by line with the use of NVivo (Lumivero) and thematically analyzed. Simultaneously, systematic reviews (SRs) of fathers’ experiences of FICare and their MH outcomes will be conducted. The study was approved by the National Research Ethics Committee (22/EM/0140) in August 2022. A parent advisory group was formed to advise on the study methodology, materials, involvement of participant parents, and dissemination of study findings.

**Results:**

A recent SR demonstrated that data saturation is likely to be achieved by interviewing 9 to 17 participants. We will study a maximum of 20 parents of infants born at less than 33 weeks’ gestation in each phase. As of October 2023, the study was ongoing. The SR studies are registered with the PROSPERO database (324275 and 306760). The projected end date for data collection is July 2024; data analysis will be conducted in November 2024 and publication will occur in 2025.

**Conclusions:**

The study aims to demonstrate the feasibility of using a father or partner-sensitive FICare model for parents of premature babies with a positive impact on their MH. It will demonstrate the feasibility of providing FICare to extremely premature babies receiving intensive care. This study may support the development of inclusive FICare guidelines for nonbirthing parents and their extremely premature infants.

**Trial Registration:**

ClinicalTrials.gov: NCT06022991; https://classic.clinicaltrials.gov/ct2/show/NCT06022991

**International Registered Report Identifier (IRRID):**

DERR1-10.2196/53160

## Introduction

In 2019, in England and Wales, 49,489 premature births were recorded, and the majority would have required a neonatal unit (NU) admission [1]. Scientific and technological advancements have led to significant reductions in mortality and morbidity for preterm infants [2], and now the importance of decreasing psychosocial morbidity for the family unit is being addressed. Admission of a critically ill baby to the NU is a deeply traumatic time for parents and may result in parental mental health (MH) difficulties during and after discharge [3,4]. Studies exploring paternal experiences in the NU highlight fathers feeling neglected and in a unique position of stress, trying to balance work and home life to allow the mother to focus on their sick baby [5]. As paternal and maternal MH are closely linked, supporting the fathers could also positively impact maternal MH [6,7]. A recent study has shown reduced paternal stress in relation to the provision of family integrated care (FICare) in single-family rooms, but it only included parents of babies who did not require intensive care [8].

FICare in the NU means that parents are partners and collaborators in the care of their hospitalized baby, rather than observers or visitors. They are included in decision-making and supported to feed, clean, and hold their baby as well as learning how to provide neurodevelopmental care [9,10]. FICare studies that have focused on mothers and infants demonstrate improved neurodevelopmental outcomes [11], improved breastfeeding rates [12], reduced infection rates, and improved maternal MH [13,14]. There is a paucity of similar research regarding fathers [15]. The impact of parental MH on children is a focus of the UK government’s “First 1000 days of life” paper [16]. Implementation and improvements to FICare as a method of enhancing “parenting opportunity” are also highlighted in the National Neonatal Critical Care Review in England [17]. Synthesizing the evidence base surrounding the impact of paternal engagement addresses recommendations from National Health Service (NHS) England, the Cross Government 1001 Critical Days Campaign [7], the Neonatal Critical Care Transformation Review, and Care Quality Commission standards to increase the evidence base to support women and their families experiencing perinatal MH problems. This area currently costs the NHS an estimated £1.2 billion (equivalent to US $1.5 billion) per year [16,17]. The UK government has recently recognized the importance of maternal and paternal presence for babies in the NU via the Neonatal Care (Leave and Pay) Act, which achieved royal assent in May 2023 granting parents up to an additional 12 weeks of leave [18]. Hence, we developed a study protocol to investigate and enhance fathers’ or partners’ involvement in FICare and its impact on their MH.

This study will be the first to report on fathers’ experiences of FICare in the NU with extremely premature babies. It will broaden the field of FICare research with respect to fathers from diverse social and cultural backgrounds and will highlight the needs of fathers in the NU. Therefore, it will demonstrate the value of designing a father- or partner-sensitive FICare program. This study will also generate evidence for the feasibility of the introduction of FICare from day 1 while preterm babies are receiving intensive care.

From here on, although the study refers to “fathers,” all second parents of any gender or relationship status are included under this term throughout the remaining text.

## Methods

### Aims

This study aims to undertake an in-depth longitudinal study of the engagement of fathers or partners in FiCare and their experience and MH from NU admission to 6 weeks postdischarge of their premature baby born at 22 to 33 weeks’ gestation.

### Objectives

Our objectives are to (1) assess baseline fathers’ experiences in the NU, their involvement in FICare, and MH status during babies NU admission up to 6 weeks postdischarge, (2) conduct systematic reviews (SRs) of published papers on “Fathers and FiCare in NU” and “Fathers’ MH in the NU,” (3) develop a program to enhance the involvement of fathers in FiCare, and (4) introduce the program developed to enhance fathers’ involvement in FiCare and explore their experiences and effects on their MH.

### Outcomes

The primary outcome is paternal MH (stress) assessed by semistructured interviews.

The secondary outcomes are (1) maternal stress, assessed by the Parental Stressor Scale: Neonatal Intensive Care Unit (PSS:NICU) questionnaire; (2) paternal stress, assessed by the PSS:NICU questionnaire; (3) parental anxiety, assessed by the Generalized Anxiety Disorder Assessment-7 (GAD-7); (4) parental depression, assessed by the Personal Health Questionnaire-9 (PHQ-9); and (5); paternal engagement with FICare, assessed via interviews.

### Study Design

This is a prospective, multicenter, and multiphase study. Phase 1 will assess baseline fathers’ experiences in the NU, their involvement in FICare, and MH status during babies’ NU admission up to 6 weeks postdischarge. Simultaneously, an SR of fathers’ involvement in FICare and their MH outcomes will be conducted. A program to enhance the involvement of fathers in FICare will be developed using information from the phase 1 study, SR, existing DadPad or Imperial Family Delivered Neonatal Care app, and advice from the parent advisory group (PAG). In the phase 2 study, an enhanced father involvement program in FICare will be implemented and similar assessments as in phase 1 will be conducted (Figure 1). We will provide regular debrief sessions, and research updates or newsletters to keep staff engaged and supportive of the project. This support will be continued throughout the study.

This study has been registered with clinicaltrials.gov (NCT06022991) [19].

**Figure 1 figure1:**
[figure not shown]
Participant flow chart. FICare: family integrated care; GAD-7: Generalized Anxiety Disorder-7; NU: neonatal unit; PHQ-9: Patient Health Questionnaire-9; PSS:NICU: Parental Stressor Scale: Neonatal Intensive Care Unit.

### Systematic Reviews

The SR studies have been registered on the PROSPERO database (324275 [20], 306760 [21]) and will follow a similar methodology. A literature search of health care databases including EMBASE, EMCARE, CINAHL, Medline, BNI, PYCHInfo, and Psychology and Behaviour, and a gray literature search will be conducted. Two independent researchers will screen the results at the title and abstract level against the eligibility criteria (Table 1), with mediation by a third researcher available for any disagreements to reevaluate the paper and come to a team agreement. The matrix method will be used for data extraction [22].

**Table 1 table1:** Eligibility criteria for the systematic reviews.

	Fathers’ mental health in the NU^a^ [18]	Fathers and FICare^b^ in the NU [19]
Studies published from January 1, 2000, to October 14, 2022	✓	✓
Full paper available in English	✓	✓
Study setting is the NU	✓	✓
At least 5 study participants	✓	✓
At least half of the participants are fathers	✓	✓
Addressed paternal mental health	✓	
Addressed FICare		✓

^a^NU: neonatal unit.

^b^FICare: family integrated care.

### Study Centers

The study will be conducted at a tertiary NU (level 3) and a local NU (level 2), as defined by the Department of Health [23], in East London, United Kingdom. Average annual admissions are approximately 900 and 600 respectively, with parents from diverse ethnic and socioeconomic backgrounds. Both level 3 and 2 NUs are selected to show the feasibility of delivering enhanced father involvement in FICare in all NUs and the study findings are applicable to all levels of NUs. Although FICare culture is practiced at both sites, a formal program and expectations of FICare are not implemented.

### Clinical Staff Involvement

The wider multidisciplinary team was consulted in the study design and consideration of phase 2 study materials. They included physiotherapists, clinical psychologists, occupational therapists, dieticians, and speech and language therapists along with neonatal nursing input. The London neonatal network care coordinator was also consulted regarding the study design and implementation.

### Patient and Public Involvement

Patients and the public were involved in the design, conduct, reporting, and dissemination plans of the study. A PAG consisting of parents of preterm infants was developed. They consisted of a diverse socioeconomic and cultural mix of 4 fathers and a mother who had experienced the admission of their premature baby in the NU within the last 4 years. The PAG was involved in developing the study design. The PAG has reviewed and provided feedback on study materials, for example, participant information leaflet. A lay member is included as a coinvestigator (JB, Director of Inspire Cornwall CIC’s Neonatal DadPad) of the study.

The PAG was consulted to advise on the burden of intervention and the time required to participate in the research. This has influenced the frequency of questionnaire administration and locations of interviews and focus groups. They will support the development of appropriate phase 2 materials for the information booklet, workbook, and education sessions. The PAG will also support the dissemination of the study findings to research participants, related charity bodies (eg, Bliss), and the wider neonatal community. 

### Study Participants and Recruitment

Parents of preterm infants will be recruited to the study.

#### Inclusion Criteria

The inclusion criteria are as follows: (1) parents of 22^+0^ to 32^+6^ weeks preterm infants; (2) infants aged 1 to 7 days; (3) infants with 2 primary caregivers (the father’s or partner’s participation in the study is a must, and participation from both parents is ideal), and (4) the parents should have conversational English.

#### Sample Size

The sample size of the study is estimated based on qualitative study outcomes. A recent SR of qualitative study demonstrated that to achieve data saturation we need to interview 9 to 17 participants [24]. A focus group of 5 to 7 participants would be enough for in-depth conversations and 2 or more groups would increase the chances of successful data output [25].

In the first and second phases, up to 20 parents will be recruited (until the fathers’ interviews reach data saturation). With a father and mother each, there could be 40 participants per phase. In total, there could be 80 participants in the study.

### Phase 1 Study: Baseline Data Collection (9 Months)

#### Overview

Phase 1 will be conducted as follows: (1) Prior to the introduction of the study to wider NU clinical staff members, staff knowledge, experiences, and opinions about the role of fathers and FICare will be assessed by a questionnaire. (2) Once a parent is recruited, the PSS:NICU [26] and MH questionnaires (GAD-7 [27] and PHQ-9 [28]) will be given to complete within 7 days. (3) Fathers or partners will be invited to participate in 2 semistructured interviews, within 2 weeks of recruitment and immediately prior to discharge. The interviews will explore their MH, experiences of bonding with baby, understanding the neonatal environment, and reflecting on their service expectations. Based on the father’s or partner’s preference, interviews will be undertaken either in a private room on the NU or digitally via MS Teams at a mutually convenient time. Interviews will be digitally recorded and are anticipated to last up to 1 hour. Data saturation is expected at around 12-15 fathers. (4) The parents will be asked to complete the PSS:NICU, GAD-7, and PHQ-9 questionnaires at 3 weekly intervals, finishing on the week of discharge, to monitor their MH through their NU stay. (5) Up to 4 groups of 5 mothers will be invited to participate in a focus group to assess their wellbeing, experience of the NU, and their perspective on support for and from their partners. This will occur in a room in the NU at a time convenient to the mothers. Groups will be organized until data saturation is reached. (6) Telephone interviews and emailed questionnaires will be completed by parents at 4-6 weeks postdischarge to assess family confidence and bonding after NU discharge.

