#### Description of Questionnaires Used

##### PSS:NICU Questionnaire

The PSS:NICU was originally developed in 1993 [26]. It assesses neonatal intensive care unit–specific stressors on a Likert scale. Each item can be scored from 0 to 5, with a maximum total score of 230 over the 46 items. Modified versions exist, but the original full-length questionnaire will be used for this study as all subsections are of interest with changes to be implemented. 

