### Questionnaires

For descriptive statistics, the median and mode scores of the PSS:NICU, GAD-7, and PHQ-9 will be used to describe the outcome of the questionnaires. For inference analysis, the difference in median for the PSS:NICU, GAD-7, and PHQ-9 at admission, discharge, and 6 weeks postdischarge will be compared between phase 1 and phase 2 using the Mann-Whitney test and the paired 2-tailed *t* test. The data will be checked for outliers and these will be corrected or removed. However, where these outliers are accurate, a nonparametric statistical analysis will be performed. Depending on the data type, missing data will be replaced with mean, median, or mode. In addition, regression and multiple imputations analysis will also be used to impute or generate missing values.

Staff survey questionnaire responses to individual questions will be presented as a percentage of individuals responding yes or no. The percentage of “yes” responses to each question by the staff at the start and end of the study will be compared by paired *t* test.

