## Discussion

This study will test the hypothesis that if fathers are facilitated to engage more with their baby on the NU and are better supported during the neonatal stay, both parents will experience fewer MH symptoms during their baby’s hospitalization and up to 6 weeks postdischarge. Improving parents’ MH is shown to allow greater parent-child bonding [32] and more sensitive responsiveness of mothers to their infants’ cues [33]. Mothers engaged in the FICare model have greater confidence in caregiving at the point of discharge and seek less medical support after discharge [32]. It is anticipated that these results will translate to fathers or partners.

Unlike many other studies [12,33], this study includes parents of a wide gestational age range of premature infants, including extremely premature infants and those who are invasively ventilated and at the highest risk of adverse outcomes. This is vital as research has found that fathers find the fragile appearance of their premature infants causes significant stress [34]. A focus of the study methods will be to upskill NU staff to increase awareness and understand the importance of father engagement in FICare and their MH as well as the impact on mother and child, which is in line with the NHS Long Term Plan [17].

Limitations of the study include the need for conversational English. This is required to be able to complete the standardized questionnaires, participate in the interviews and focus groups, and to be able to engage with the phase 2 provisions. The language for the phase 2 materials will be kept as simple to ensure readability and understanding. Exclusion from recruitment based on language will be monitored. The perceived research burden may disproportionately impact parents who have older children, have a greater distance to travel, limited parental leave, or who do not have English as their first language. There may also be cultural barriers to overcome when discussing MH.

A prospective cohort study was the most practical and ethical study design. The sample size and the primary outcome of the study is based on the qualitative data. A bigger sample size will be required for the study to be based on the quantitative or questionnaire data. The quantitative or questionnaire data collected in this study is to support the qualitative data and to test the feasibility of collecting such data longitudinally.

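### The aim runs to 6 weeks postdischarge, but the primary interviews end before discharge, the schedule does not name the scales sent at 4-6 weeks, and a unit-specific stress scale is compared after the family has left

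*Protocol article*

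**What the plan says.** The Objective in the Abstract sets the primary aim as the effect of supporting fathers' engagement "on their MH up to 6 weeks postdischarge". The hypothesis in the Discussion has the same horizon for both parents: "hospitalization and up to 6 weeks postdischarge".

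The Outcomes section states: "The primary outcome is paternal MH (stress) assessed by semistructured interviews". It gives no time point. PSS:NICU, GAD-7 and PHQ-9 are secondary, and PSS:NICU is the only one of the three assigned to stress.

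The Phase 1 Overview sets the assessments:

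- Item (3), interviews: "Fathers or partners will be invited to participate in 2 semistructured interviews, within 2 weeks of recruitment and immediately prior to discharge".
- Item (4), the three named scales: "questionnaires at 3 weekly intervals, finishing on the week of discharge", with the purpose of following mental health during the stay on the unit.
- Item (6), after discharge: "Telephone interviews and emailed questionnaires will be completed by parents at 4-6 weeks postdischarge to assess family confidence and bonding after NU discharge". The questionnaires are not named.

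Phase 2 repeats the phase 1 assessments. The Questionnaires section under Statistical Analysis then compares all three scales between phases "at admission, discharge, and 6 weeks postdischarge". The Methods paragraph of the Abstract also runs the three scales from admission to 6 weeks postdischarge. Of PSS:NICU the protocol says: "It assesses neonatal intensive care unit–specific stressors on a Likert scale".

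**The concern.** A conclusion about mental health after discharge needs a measurement after discharge, by an instrument that fits that period. The interview schedule does not show one for the primary outcome. For the scales, the schedule and the analysis differ on what is collected and when. For PSS:NICU, the analysis uses a time point at which the stressors being rated are no longer present.

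If this stays as written, a report could claim an effect on paternal stress to 6 weeks postdischarge when the primary instrument was last used just before discharge, and when the only stress questionnaire asks about a place the family has left.

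**Working it through.** No sample size, power or error rate is involved. The check sets time points and instruments side by side.

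**1. Primary outcome.** The aim and hypothesis reach 6 weeks postdischarge. Semistructured interviews are scheduled within 2 weeks of recruitment and immediately before discharge, so 2 of 2 fall before discharge. The 4-6 week telephone interview is not called semistructured and is assigned to confidence and bonding. Because phase 2 follows phase 1, this applies to both sides of the comparison.

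**2. The three scales.**

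| Source | Last time point for PSS:NICU, GAD-7, PHQ-9 |
|---|---|
| Phase 1 Overview, item (4) | week of discharge (three-weekly series) |
| Phase 1 Overview, item (6) | 4-6 weeks, questionnaires not named |
| Abstract, Methods | 6 weeks postdischarge |
| Questionnaires (analysis) | 6 weeks postdischarge |

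The analysis can be carried out only if the unnamed emailed questionnaires are these scales. The schedule does not say that they are.

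**3. Does each scale fit the postdischarge contact?** GAD-7 and PHQ-9 each look back 2 weeks, according to their descriptions. The period covered by a form completed t weeks after discharge is t - 2 to t:

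- t = 4: weeks 2 to 4 after discharge
- t = 6: weeks 4 to 6 after discharge

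Both periods lie wholly after discharge, so these scales can be interpreted anywhere in the window. PSS:NICU rates stressors of the unit, and the protocol gives no recall instruction or adaptation for use at home. A score at 4-6 weeks is therefore at best a retrospective rating of the stay.

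**4. Extent.** The PSS:NICU comparison at that time point is 1 scale x 1 time point x 2 parents = 2 between-phase comparisons, if fathers and mothers are analysed separately.

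**5. Time label.** The contact window is 4-6 weeks and the analysis label is 6 weeks. The window is the same in both phases, so by design it creates no difference between them. The label is still inexact.

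**6. Room to change the conduct.** The Results section reports 22 families recruited by October 2023, against a ceiling of 20 per phase. If that ceiling was kept, at least 22 - 20 = 2 families belong to phase 2. Most or all of phase 1 has therefore probably been recruited, and a new procedure would fall mainly or only on phase 2.

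**The case against.** A reader might infer that the mental health questionnaires stop at discharge, that the study can give no answer at 6 weeks, and that every comparison there is lost: 3 scales x 1 time point x 2 parents = 6 of 18 (3 x 3 x 2). The document does not support this. The wording that ends the series is tied to monitoring during the stay and can be read as closing only the in-unit series. Item (6) provides for emailed questionnaires, the only parent questionnaires described anywhere are these three, and the Abstract says that they run to 6 weeks. The participant flow figure is not available here, but its legend abbreviates all three. The likeliest intention is that the same scales are emailed. GAD-7 and PHQ-9 would then give valid postdischarge data.

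On the interviews, it is fair to say that no time point is fixed for the primary outcome, that the Abstract gives one span for interviews and questionnaires together, and that the in-unit interviews cover mental health and bonding together. A stated purpose of bonding does not prove that stress is left out of the later call. The topic guide is not shown, and an article may leave it to the full protocol.

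Finally, the Discussion calls the questionnaire data supportive and a test of feasibility.

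These points remove any claim that the data are absent. They do not remove three others. The schedule, Abstract and analysis need reconciling. The primary outcome has no stated postdischarge assessment by its own instrument. And PSS:NICU after discharge is hard to interpret on any reading; if the Abstract is right that it is given at 6 weeks, that difficulty is confirmed. The supportive status of the questionnaires does not touch the second point, which concerns the primary outcome.

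**Conclusion.** The concern stands in a limited form. As written, the primary interview outcome supports a conclusion up to discharge, not to 6 weeks after it. The postdischarge mental health conclusion can rest on GAD-7 and PHQ-9 as supportive data, provided these were in the emailed pack. The PSS:NICU comparison after discharge, 2 comparisons if parents are analysed separately, should not be read as current stress. As PSS:NICU is the only questionnaire for stress, what remains after discharge concerns anxiety and depression.

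This rests on two assumptions: that item (6) describes the call fairly, and that no retrospective instruction for PSS:NICU exists in material not shown. If the call covered paternal stress in the same way in both phases, the limit on the primary conclusion falls away. The point about PSS:NICU as current stress would remain.

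**What to change.** Four changes, all to wording or to the reading of results:

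1. Make discharge the last PSS:NICU comparison, or label any later score as a retrospective rating of the unit stay.
2. Name the scales in the 4-6 week pack. State that it contains GAD-7 and PHQ-9 for both parents in both phases, once confirmed against what phase 1 families were sent, and rest the postdischarge conclusion on these as supportive data.
3. Limit the primary interview conclusion to the period up to discharge, unless the 4-6 week call covered paternal stress in the same way in both phases.
4. Relabel the 6-week analysis as 4-6 weeks and keep the same window in both phases.

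Do not move the pack to 6 weeks or add stress topics to the call for phase 2 alone. With recruitment this far on, either step would confound timing or content with phase. A days-since-discharge covariate would not repair it: it would be correlated with phase, in about 20 families per phase, and the planned Mann-Whitney test takes no covariate.

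The cost is the 6-week PSS:NICU comparison and a primary conclusion narrower than the stated aim. No contact or form is added.
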